### **7.3 Follow-up of adverse events**

All adverse events will be followed until they have abated, or until a stable situation has been reached. Depending on the event, follow up may require additional tests or medical procedures as indicated, and/or referral to the general physician or a medical specialist.

## 8. STATISTICAL ANALYSIS

### 8.1 Univariate analysis

Baseline characteristics as described in par 6.1.2 will be presented and between group differences will be studied to determine whether groups are comparable at baseline.

When these data are not normally distributed, non parametric wilcoxon signed rank sum test will be used. When the data are normally distributed student t-test will be used. The  $\alpha$  will be set at 0,05.

### 8.2 Multivariate analysis

The main outcomes as described in par 6.1.1 will be compared between the intervention and control group at the different timepoints using multilevel regression analysis. Time, group, location and possible significant baseline values will be added to the model.

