## 1. INTRODUCTION AND RATIONALE

The annual rate for first ever stroke in the Netherlands is estimated about 41.000 persons, with a prevalence of about 216.500. The costs incurred by the care of stroke patients are extremely high and are estimated to exceed one billion Euros in the Netherlands. A recent analysis of initial and secondary care costs of Stroke in the United Kingdom showed that inpatient rehabilitation accounted for about 44% of all costs. In addition, a recent meta-analysis involving 14 trials (1957 patients) has shown that early supported discharge (ESD) with additional services in the community is beneficial in optimizing the transition from the rehabilitation setting to independent living and cost-effective by reducing the length of stay (LOS) of inpatient services and long term dependency of stroke patients. Several RCT's and longitudinal studies have shown that ESD is enabled as soon as patients are independent in their transfers and gait, suggesting that ESD is heavily dependent on balance and motor control of the lower limb. Exercise therapy typically focuses on restoring and/or improving motor function and performance of activities of daily living with the aim to enhance independence. Several systematic reviews have indicated that additional exercise therapy and repetitive task training have a significant effect on functional outcome after stroke, concluding that that more exercise therapy is better.

Guidelines in the Netherlands conclude therefore that patients who are in a rehabilitation setting should have the opportunity to receive a minimal dose of 40 to 60 minutes exercise therapy. In the same vein, the UK guidelines in the United Kingdom recommends a daily dose of 45 minutes of exercise therapy in the early stages after stroke.

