Outcome measures will be measured at baseline prior randomization, after the eight week intervention period and again after 12 weeks (follow up) by a blinded assessor who is not involved in training. Length of stay in the rehabilitation center will be reported at discharge of the patient. Self reports in the (cost)diary will take place during the intervention. To assess the long term costs, some patients will be asked to keep the cost diary until the end of the study in 2016. These data will be obtained by the blinded assessor with telephone interviews.

In addition, at the end of the intervention, semi-structured interviews will be conducted with some patients and caregivers to collect qualitative data regarding the experience of CME.

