### **6.1.2 Other study parameters**

Patient and caregiver characteristics will be recorded. Of the patient we will document: age, type of stroke, date of stroke, hemiplegic side, sensory deficits (yes/no), hemianopia (yes/ no) and neglect (yes/no). Of the caregiver we will record: age, relation to patient, work (yes/no), duration of partnership and existing morbidities

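### Section 8.2 secures no prognostic covariate for length of stay, although the likely predictors of discharge are measured before randomisation

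*Protocol*

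**What the plan says.** Protocol section 8.2 sets one analysis for all outcomes of section 6.1.1: "The main outcomes as described in par 6.1.1 will be compared between the intervention and control group at the different timepoints using multilevel regression analysis". Its model terms are given in one sentence: "Time, group, location and possible significant baseline values will be added to the model". It does not define *significant*, and it does not list the candidate baseline values.

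The only baseline comparison described is in section 8.1, at alpha 0.05: "Baseline characteristics as described in par 6.1.2 will be presented and between group differences will be studied to determine whether groups are comparable at baseline". For the patient, section 6.1.2 lists "age, type of stroke, date of stroke, hemiplegic side, sensory deficits (yes/no), hemianopia (yes/ no) and neglect (yes/no".

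Length of stay is the item labelled primary in section 6.1.1, and section 8.3 also calls it the primary outcome. (The Summary puts the Stroke Impact Scale beside it.) It runs from admission to discharge and is reported once, at discharge.

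On what drives discharge, section 1 points to independence in transfers and gait, "suggesting that ESD is heavily dependent on balance and motor control of the lower limb". Section 6.1.1 lists measures of these: the Rivermead Mobility Index, Barthel Index, walking tests, Berg Balance Scale, Fugl-Meyer leg score and Motricity Index. On timing it states: "Outcome measures will be measured at baseline prior randomization".

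**The concern.** Most outcomes in section 6.1.1 have a baseline score of their own that could serve as a covariate. Length of stay cannot have one. A rule to adjust each outcome for its own baseline value would therefore still leave it without a patient-level predictor, so this outcome needs a covariate chosen for it by name.

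The protocol's rationale identifies plausible candidates, and the trial collects them before allocation. The analysis sections do not connect the two: the list that section 8.1 compares leaves out motor function, and section 8.2 leaves entry to an unspecified significance rule. Two things are at stake in a small trial:

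- residual variance that could be removed at almost no cost;
- an estimate not conditioned on how the arms happen to differ in baseline mobility or balance.

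**Working it through.** **Step 1. What section 8.2 fixes for length of stay.**

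| Term in 8.2 | Applies to length of stay? |
|---|---|
| Time | No: one value per patient, recorded at discharge |
| Group | Yes |
| Location | Yes |
| Significant baseline values | Undefined; no variable named |

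**Step 2. The baseline list compared in 8.1.** Section 6.1.2 gives seven patient variables. None measures balance, transfers, gait, leg strength or daily activities. Hemiplegic side records laterality, not severity.

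**Step 3. What a significance rule would do.** Suppose *significant* means a between-group test at 0.05; the protocol does not say so. Under randomisation each variable then enters with probability of about 0.05, whatever its prognostic value. With seven variables, taken as independent, none enters in 0.95^7 = 0.698, or about 70% of trials.

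**Step 4. Precision.** The protocol gives neither an SD for length of stay nor a correlation with baseline function, so there is no figure of its own to reproduce here. Assume a within-setting correlation r of 0.3 to 0.6 on the log scale. Section 4.3 plans 30 patients per arm before the dropout allowance, so take 60 evaluable patients. Adjustment multiplies residual variance by 1 − r², and the equivalent unadjusted number is 60/(1 − r²).

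| r | 1 − r² | Fall in residual variance | Equivalent N |
|---|---|---|---|
| 0.3 | 0.91 | 9% | 65.9 |
| 0.4 | 0.84 | 16% | 71.4 |
| 0.5 | 0.75 | 25% | 80.0 |
| 0.6 | 0.64 | 36% | 93.8 |

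**Step 5. Power.** Assume a true effect of 0.5 SD, the same in all three settings, with 10 patients per arm per setting. Simulation (4000 runs) compared a model with group and location against the same model plus the baseline score.

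| r | Group and location | Plus baseline score | Gain (points) |
|---|---|---|---|
| 0.3 | 48.6% | 51.7% | 3.1 |
| 0.5 | 48.2% | 59.7% | 11.5 |
| 0.6 | 47.2% | 65.2% | 18.0 |

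The first column should be the same in every row; the differences are simulation error, since one standard error is √(0.5 × 0.5/4000) = 0.8 points.

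**Step 6. Chance imbalance.** With 30 per arm, the between-arm difference in a standardised baseline score has SD √(2/30) = 0.258. The probability that it exceeds 0.3 SD in either direction is 0.245. At r = 0.5, an imbalance of 0.3 SD shifts the unadjusted length-of-stay difference by 0.5 × 0.3 = 0.15 SD. The unadjusted standard error already allows for this on average over randomisations. Adjustment would remove it from the estimate in the trial actually run.

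**The case against.** A reader might infer that the motor predictors will go unused because section 8.1 restricts what enters the model. The documents do not support that. Section 8.2 makes no reference to 8.1 or 6.1.2; its only cross-reference is to 6.1.1, where the motor scales are listed, and its wording on baseline values is open. A baseline Berg or Rivermead score could enter. The link from the tests in 8.1 to the model in 8.2 is a likely reading, but it is not written. This part of the objection stands.

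A reader might also infer bias. That does not hold either: under randomisation a model with group and location is unbiased, and its type I error already covers chance imbalance. Tabulating or testing a score in 8.1 would not change the estimate. This stands too.

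The size is open to challenge. Both r and the 0.5 SD effect are assumed. Section 1 hypothesises 1 day in the hospital stroke unit and 7 days in the rehabilitation centre and nursing home, so a common effect is a simplification. The eligibility limits on walking score and planned discharge home narrow the functional range and could weaken the correlation. Section 1 only suggests the dependence and gives no strength of association. All of this stands, and it is why the small gain at r = 0.3 belongs in the range.

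Finally, covariate lists are often left to a statistical analysis plan, and the trial describes itself as a pilot. If the protocol were silent, that would be a full answer. But it states a covariate rule, and that rule makes the adjustment of the outcome marked primary depend on an undefined significance criterion. That is a choice badly fixed, not merely a detail deferred.

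**Conclusion.** The point holds in a limited form. For length of stay, section 8.2 fixes only group and location and leaves any prognostic covariate to an undefined criterion. The one baseline list that the protocol says it will compare omits motor function, although the rationale suggests that early discharge depends on it and the trial measures it before randomisation. The predictors are not secured; whether they would in fact be left out cannot be told from the text.

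The consequence is avoidable loss of precision and no conditional protection against chance imbalance. Over the assumed range of r the gain forgone is about 3 to 18 points of power at the assumed effect. The direction of the gain relies only on a baseline motor score being related to length of stay within settings; its size cannot be derived from the protocol.

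**What to change.** In section 8.2, prespecify a separate length-of-stay model with group, location and one named baseline motor score that is already collected, for example the Berg Balance Scale or the Rivermead Mobility Index, entered whatever its significance. Days from stroke to randomisation, available from the recorded stroke date, could be added in the same way.

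In section 8.1, add the baseline functional scores to the baseline table. This is for description only; it does not replace the change in 8.2.

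The cost is one sentence in each section and one degree of freedom per covariate, with no new data, patients or visits. If the chosen score turns out to be weakly related to length of stay, little more than that degree of freedom is lost.

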### 8.3 Cost-effectiveness analysis

A cost effectiveness and a cost-utility analysis will be performed The primary outcome of the trial, length of Stay, in combination with the information of the cost diary will be used in the cost effectiveness analysis. Unit costs will be taken from national sources.

In the costs utility-analysis the outcome measure is quality-adjusted life-years (QALYs) based on the Dutch tariff for the Euro(QoI).

## 9. ETHICAL CONSIDERATIONS

### 9.1 Regulation statement

The study will be conducted according to the principles of the Declaration of Helsinki 59th WMA General Assembly (Seoul, October 2008) and in accordance with the Medical Research involving Human Subjects Act (WMO).

### 9.2 Recruitment and consent

In the first week of admittance in one of the participating centres, every patient with stroke will be screened by their own treating medical specialist to evaluate if participation in this study is possible. Eligible patients and their chosen caregiver will be informed in an interview with the primary researcher and a therapist will judge if the caregiver can adequately assist the patient during exercises. A reflection period will follow. Upon inclusion, a second interview with the primary researcher will follow and informed consent will be signed. Next the baseline measurements will be done. Randomisation will follow and treatment starts as soon as possible after that.

### 9.3 Benefits and risks assessment, group relatedness

When the CARE4STROKE programme is followed patients will have a surplus of 150 minutes of training a week. Literature shows this to be beneficial for functional outcome after stroke. Next to that caregivers will be involved and will most likely feel in control because they can help. This may lower their experienced strain.

The exercise programme can be tailor made for the patient and caregiver by the therapist. Given the experience gained in the pilot study, the intervention can be considered as safe for both patients and caregivers. The small risk of adverse events will be minimized since a therapist will judge if the caregiver can adequately assist the patient during exercises before inclusion. In addition, safety instructions are provided in the app and there is a close guidance of a therapist during the intervention period. Also instructions are described what to do in case of an adverse event. The control group will have no additional benefit or risks. Assessments will take place at baseline, after the intervention and at twelve weeks post randomisation. They consist of questionnaires and tests, taking approximately two hours per assessment.

#### **9.4 Compensation for injury**

The sponsor/investigator has a liability insurance which is in accordance with article 7, subsection 6 of the WMO.

Each participating centre has an insurance which is in accordance with the legal requirements in the Netherlands (Article 7 WMO and the Measure regarding Compulsory Insurance for Clinical Research in Humans of 23th June 2003). This insurance provides cover for damage to research subjects through injury or death caused by the study.

1. € 450.000,-- (i.e. four hundred and fifty thousand Euro) for death or injury for each subject who participates in the Research;
2. € 3.500.000,-- (i.e. three million five hundred thousand Euro) for death or injury for all subjects who participate in the Research;
3. € 5.000.000,-- (i.e. five million Euro) for the total damage incurred by the organisation for all damage disclosed by scientific research for the Sponsor as 'verrichter' in the meaning of said Act in each year of insurance coverage.

The insurance applies to the damage that becomes apparent during the study or within 4 years after the end of the study.

#### **9.5 Incentives (if applicable)**

Subjects will not receive special incentives or additional treatments next to the assigned intervention during their participation in this study. Any travel costs incurrent for participation will be reimbursed.

## **10. ADMINISTRATIVE ASPECTS AND PUBLICATION**

### **10.1 Handling and storage of data and documents**

All research data will be stored in Reade, center for rehabilitation and rheumatology. The data will be kept 15 years. All research files will have a code, which makes the file anonymously. Only the research team is able to trace the data to the individual subjects by using a subject identification code list. The outcome measurements can also be reported in the medical file of the patient when he/ she gives his/ her consent.

### **10.2 Amendments**

Amendments are changes made to the research after a favourable opinion by the accredited METC has been given. All amendments will be notified to the METC that gave a favourable opinion.

### **10.3 Annual progress report**

The sponsor/investigator will submit a summary of the progress of the trial to the accredited METC once a year. Information will be provided on the date of inclusion of the first subject, numbers of subjects included and numbers of subjects that have completed the trial, serious adverse events/ serious adverse reactions, other problems, and amendments.

### **10.4 End of study report**

The investigator will notify the accredited METC of the end of the study within a period of 8 weeks. The end of the study is defined as the last patient's last visit.

In case the study is ended prematurely, the investigator will notify the accredited METC, including the reasons for the premature termination.

Within one year after the end of the study, the investigator/sponsor will submit a final study report with the results of the study, including any publications/abstracts of the study, to the accredited METC.

### **10.5 Public disclosure and publication policy**

All the publications of this study will be public.

